## Abstract

**Background:**

Excessive weight gain is commonly observed within the first year after kidney transplantation and is associated with negative outcomes, such as graft loss and cardiovascular events. The purpose of this study is to evaluate the effect of a high protein and low glycemic-index diet on preventing weight gain after kidney transplantation.

**Methods:**

We designed a prospective, single-center, open-label, randomized controlled study to compare the efficacy of a high protein (1.3–1.4 g/kg/day) and low-glycemic index diet versus a conventional diet (0.8–1.0 g/kg/day of protein) on preventing weight gain after kidney transplantation. A total of 120 eligible patients 2 months after transplantation will be recruited. Patients with an estimated glomerular filtration rate through the modification of diet of renal disease (MDRD) formula < 30 mL/min/1.73 m^2^ or urinary albumin excretion > 300 mg/24 h will be excluded. Patients’ diets will be allocated through simple sequential randomization. Patients will be followed-up for 12 months with nine clinic appointments with a dietitian and the evaluations will include nutritional assessment (anthropometrics, body composition, and resting metabolic rate) and laboratory tests. The primary outcome is weight maintenance or body weight gain under 5% after 12 months. Secondary outcomes include body composition, resting metabolic rate, satiety sensation, kidney function, and other metabolic parameters.

**Discussion:**

Diets with higher protein content and lower glycemic index may lead to weight loss because of higher satiety sensation. However, there is a concern about the association of high protein intake and kidney damage. Nevertheless, there is little evidence on the impact of high protein intake on long-term kidney function outcome. Therefore, we designed a study to test if a high protein diet with low-glycemic index will be an effective and safe nutritional intervention to prevent weight gain in kidney transplant patients.

**Trial Registration:**

ClinicalTrials.gov identifier, NCT02883777. Registered on 3 August 2016.

**Electronic supplementary material:**

The online version of this article (doi:10.1186/s13063-017-2158-2) contains supplementary material, which is available to authorized users.

## Background

Weight gain after kidney transplantation is very often observed and it has been reported to be between 10% and 35%, mainly during the first year after transplant [1–4]. Post-transplant overweight and obesity may lead to negative post-transplant outcomes, such as graft loss and cardiovascular events [5, 6]. In addition, weight gain during the first year post-transplantation appears to be a risk factor for the development of new-onset diabetes and metabolic syndrome [7–9]. The main factors implied in the weight gain in this population are the immunosuppressive regimen, the cessation of dietary restrictions associated with dialysis, consequent appetite restoration, and improvements in quality of life [10, 11].

Data on nutritional management to prevent weight gain after transplantation is scarce [12–17]. Moreover, the evidence assessing protein requirements in kidney transplant patients is also limited [15, 18]. High protein intake in the early period post-transplant is recommended to match protein catabolism, but there is no evidence available regarding long-term protein requirements of stable renal-transplanted recipients [18].

A high-protein diet is known to be effective for body weight loss and subsequent weight maintenance in the general population [19–22]. Protein generally exerts a better satiety effect than carbohydrates and lipids [23–25]. During the process of weight loss, a high-protein diet preserves lean body tissue, which is the major determinant of resting and 24-h energy expenditure, which, in turn, prevents a greater reduction in energy expenditure [23] usually observed in individuals undergoing a weight reduction program. Besides, it is well known that a diet with a low glycemic index (GI) is determinant of postprandial metabolic responses to food intake and also may have beneficial effects on body weight and body composition [26–28]. Larsen et al. [29] have shown that a dietary plan with moderately high protein associated with a slightly reduced GI leads to weight loss maintenance in overweight adults who had lost at least 8% of body weight. In this context, we designed a randomized clinical trial in order to evaluate the effect of a high protein and low GI diet in preventing weight gain after kidney transplantation.

## Methods/design

### Study design and centers

This is a prospective, single-center, open-label, randomized clinical trial that will include an interventional group (high protein and low GI diet) and a control group (usual diet) patients that will undergo kidney transplant at Hospital de Clínicas de Porto Alegre, Brazil. The present protocol was written in accordance with Standard Protocol Items: Recommendations for Interventional Trials (SPIRIT) guideline, completing the SPIRIT checklist, and constructing a flow diagram in order to optimize the quality of reporting [30] (Fig. 1 and Additional file 1).

**Fig. 1 Fig1:**
[figure not shown]
SPIRIT diagram. *Timepoint of the protocol: -t0, enrolment; -t1, baseline; -t2, -t3, -t4, -t5, -t6, -t7, first semester monthly appointments; -t8, month 9; -t9, month 12

### Inclusion and exclusion criteria

The study will include kidney transplant recipients who agree to participate in the study protocol and provide written informed consent. The exclusion criteria will be the following: patients younger than 18 years old, prior transplant, multiple organ transplant, type 1 diabetes mellitus, current cancer, women in pregnancy or lactation period, recipients of a kidney from living donors, patients with urinary albumin excretion > 300 mg/24 h or estimated glomerular filtration rate through the modification of diet of renal disease (MDRD) formula < 30 mL/min/1.73 m^2^, and/or anticipated difficulty of adherence (for example, due to any kind of cognitive deficits or dementia).

### Sample size

Sample size calculations were carried out in WINPEPI 11.20 (Brixton Health, Israel) based on data from Souza et al. [31]. To find a difference of 5% in body weight between groups 1 year after the transplant, considering a standard deviation of 8.8%, a significance level of α ≤ 0.05 and a statistical power of 80%, the minimum sample size will be 98 patients. Because of possible dropouts, we will include 120 patients (60 randomized to each group).

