### Primary outcome

The primary outcome will be weight maintenance and weight gain under 5% of body weight.

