### Statistical analyses

Continuous variables with normal distribution will be expressed as mean ± standard deviation. The Shapiro-Wilk test will be used for normality assessment; asymmetrically distributed continuous variables will be expressed as median and interquartile range; and categorical variables will be expressed as absolute and relative frequencies. For between-group comparisons, the Student’s *t* test will be used for normally distributed variables, and the Mann–Whitney *U* test for asymmetrically distributed variables. A paired *t* test will be used for within-group analysis of body weight and body composition. The Chi-square or Fisher’s exact tests will be used to evaluate associations between categorical variables. The generalized estimating equations test with Bonferroni adjustment will be used for comparison between variables during the study period. The significance level will be set lower than 5%, and all data will be analyzed in SPSS 20.0 (SPSS Inc., Chicago, IL, USA).

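### The 98/120 sample size and its 80% power are for a difference in mean percent body weight, but the primary outcome is stated as a per-patient threshold (gain under 5%)

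*Protocol article*

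**What the plan says.** The Sample size section of the protocol article sets out "To find a difference of 5% in body weight between groups 1 year after the transplant, considering a standard deviation of 8.8"%, with "a significance level of α ≤ 0.05" and "a statistical power of 80"%. It arrives at a minimum of 98 patients and raises this to 120, 60 per group, to cover dropouts. No proportion of patients expected to stay under any threshold is given.

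The Primary outcome section reads: "The primary outcome will be weight maintenance and weight gain under 5% of body weight". The Abstract (Methods) reads: "The primary outcome is weight maintenance or body weight gain under 5% after 12 months". The opening of the Discussion repeats the same threshold.

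The Statistical analyses section lists tests by type of variable. The t test or Mann–Whitney test is for between-group comparisons of continuous variables, and a paired t test is for within-group change in body weight. Chi-square or Fisher's "exact tests will be used to evaluate associations between categorical variables", and generalised estimating equations cover comparisons over the study period. None of these is tied to the primary outcome.

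**The concern.** The figure of 5% does two different jobs. In the sample size it is a distance between two group means. In the primary outcome it is a cut-off applied to each patient. A calculation for the first says nothing direct about the second, and reducing a continuous measurement to yes/no usually discards information.

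Two things are at stake:

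- **The stated power may not belong to the primary analysis.** A true effect of the planned size could then be missed more often than the 20% that readers will infer, and a null result could be misread as evidence that the diet does not work.
- **Two candidate primary analyses are left open.** One compares means and the other compares proportions. The trial is open-label, so the choice should not be left until data by arm can be seen.

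**Working it through.** **Inputs.** From the Sample size section: difference 5 percentage points, SD 8.8, alpha 0.05, power 80%, 98 evaluable (49 per group), 120 enrolled (60 per group). From the Primary outcome section: threshold of 5% gain. Assumptions of this check: a two-sided test (sidedness is not stated), the same SD in both groups, and a control mean gain scanned from 0% to 20%, because none is given for the sizing.

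**1. The protocol's own figure.**
n per group = 2 × (1.96 + 0.8416)² × (8.8/5)² = 48.6, so 49 per group and 98 in total. This matches. A one-sided test would give 78, so a two-sided comparison of means was evidently used. By the t test, power is 79.5% at 49 per group and 87% at 60.

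**2. The same assumptions applied to the threshold.**
With normal percent change and control mean m, the intervention mean is m − 5. The probabilities of staying under 5% are
p(control) = Φ((5 − m)/8.8) and p(intervention) = Φ((10 − m)/8.8).
The power of a two-proportion comparison, with p̄ the average of the two, is
Φ{ [ |difference| × √n − 1.96 × √(2p̄(1 − p̄)) ] / √(p₁(1 − p₁) + p₂(1 − p₂)) }.

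The best case is m = 7.5, where the threshold lies midway between the two means:
- p = Φ(−0.284) = 0.388 and Φ(0.284) = 0.612, a difference of 0.2236.
- n = 49: (0.2236 × 7 − 1.386)/0.689 = 0.26, power 60%.
- n = 60: (0.2236 × 7.746 − 1.386)/0.689 = 0.50, power 69%.
- n for 80%: (1.386 + 0.8416 × 0.689)²/0.2236² = 77.3, so 78 per group, 156 evaluable. With the loss the protocol allows (22/120 = 18.3%), that is about 191 enrolled.

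| Control mean gain | Under 5%: control v intervention | Power, 49 per group | Power, 60 per group |
|---|---|---|---|
| 0% | 71.5% v 87.2% | 48% | 57% |
| 5% | 50.0% v 71.5% | 59% | 68% |
| 7.5% | 38.8% v 61.2% | 60% | 69% |
| 10% | 28.5% v 50.0% | 59% | 68% |
| 15% | 12.8% v 28.5% | 48% | 57% |
| 20% | 4.4% v 12.8% | 31% | 37% |

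Exact enumeration in the best case gives 62% (uncorrected chi-square) and 54% (Fisher) at 49 per group, and 71% and 64% at 60 per group.

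**3. Sensitivity to shape.** The same power formula, with difference 5 and SD 8.8 kept and Φ replaced by another distribution function, gives these best cases at 49 per group: logistic 71%, t with 5 degrees of freedom 77%, gamma-type right skew of 1 about 79%. For the last two, the best case at 60 per group is 85% and 87%. These shapes are also assumptions; the protocol states none.

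**The case against.** The strongest reply is that a comparison of means may be what was intended. The stated aim is to prevent weight gain. Where the Statistical analyses section names body weight it treats it as continuous, and it also offers between-group t tests and generalised estimating equations. On that reading 98 and 80% are right and only the outcome wording is loose. This stands as a possibility. But the threshold appears in the Abstract, the Primary outcome section and the Discussion, so it is the more natural reading, and if means were intended those places misstate the primary outcome. Either way some text has to change.

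Four stronger inferences are tempting and are not supported:

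- **That power is at most 60%.** This is the best case for 98 evaluable under normality. It ignores the 69% if all 120 are analysed. It is also not a bound, since other shapes reach 71–79% at 98, and some exceed 80% with no dropout at all and a favourable control mean.
- **That the protocol prescribes chi-square or Fisher for the primary outcome.** It assigns those tests to categorical variables in general; the link is inferred.
- **That the lowest table rows are the expected ones.** The Background cites gains of 10% to 35%, but after transplantation generally, mainly in the first year. Patients enter at 2 months, so gain before entry does not count.
- **That the trial as a whole is too small.** For a difference in means it is sized as claimed.

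It is also fair to say that changing a primary outcome is more than a wording matter once 60 patients have started in an open-label trial.

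**Conclusion.** The sizing and the primary outcome do not match as written, and nothing else in the article reconciles them. The 80% belongs to a difference in mean percent body weight and is not supported for the threshold outcome.

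If the threshold is compared as proportions and percent change is normal with the planned difference and SD, the best-case chance of missing the planned effect is about 40% at 98 evaluable and about 31% at 120, against the implied 20%. It is higher when the control mean gain is far from 7.5%. How large the shortfall is depends on the distribution and on a control mean that the protocol does not give. That the power statement and the stated outcome are different quantities depends on neither.

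**What to change.** Bring the Sample size and Primary outcome sections into line, with the Abstract and Discussion to match, before any comparative look at the data. There are two ways:

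1. **Make the continuous variable primary.** State percent change in body weight from randomisation to month 12 as the primary variable, with a between-group comparison of means. The existing calculation then applies. Keep a gain under 5% as the first secondary outcome.
2. **Keep the threshold primary.** Name its test, remove the 80% claim, and restate the power with the assumed control mean and distribution: about 60% at 98 evaluable and about 69% at 120 in the best case under normality.

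Neither needs extra patients or measurements. The first costs a mid-trial amendment in an open-label trial with 60 patients already started. It should be dated and justified, and should say what had been seen by arm at that point, since one investigator takes all the measurements and the same dietitian delivers the intervention. The second costs a less favourable stated power.

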The diet prescription will be calculated using nutritional software (Nutribase 2007 Clinical Manager software version 7.14). GI will be estimated as proposed by the Food and Agriculture Organization (FAO) [33] using the international table–United States Department of Agriculture (USDA) table [34], with glucose as the standard food [35] and considering a daily glycemic load of ≤ 80 g. This will be considered as 1.3–1.4 g/kg/day of protein. Energy intake will be assessed by a 24-h recall over nine visits by the research dietitian. Diet composition also will be analyzed using the nutritional table with the software (Nutribase 2007 Clinical Manager software version 7.14) at each visit.

Two months after transplantation, patients are invited to participate in the study protocol and are randomized to the intervention or control group. The intervention group receives the study diet and the control group receives the conventional diet. Both groups visit the center once a month for the first 6 months. After that, another two visits are scheduled at months 9 and 12. At each visit both groups are submitted to the research anthropometric tests and the 24-h recall diet is completed. Besides the prescription of the intervention diet after randomization, the research dietitian reinforces diet adherence at each visit, but only for the intervention group. The standard diet adherence reinforcements are more sporadic for the control group (three to four visits scheduled per year) with the standard dietitian from the hospital. Thus, the intervention group receives eight diet reinforcements and the control group receives three to four reinforcements during the study protocol.

Food intake and adherence to the prescribed diet will be assessed by 24-h recall. An experienced registered dietitian will implement the recall during a face-to-face interview. To assure accurate answers, a photographic album of food portions and household measures will increase the precision of the amount of food consumed. A total of nine records over 1 year will be available for each included patient. Furthermore, the study protocol also includes the collection of urinary urea excretion and this adds to the calculation for the protein equivalent of total nitrogen appearance (nPNA) as a measure of dietary protein intake adherence.

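### If dropout depends on earlier weight and does so differently in the two arms, the t/Chi-square tests and ordinary GEE named for weight can be biased; a mixed model on all visit weights is a cheap improvement

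*Protocol article*

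**What the plan says.** All references are to the protocol article.

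- **Sample size.** The target is stated as "To find a difference of 5% in body weight between groups 1 year after the transplant", with SD 8.8%, α 0.05 and 80% power; "the minimum sample size will be 98 patients". The total is then raised: "Because of possible dropouts, we will include 120 patients (60 randomized to each group"). No dropout rate is given.
- **Abstract, Methods.** "The primary outcome is weight maintenance or body weight gain under 5% after 12 months".
- **Statistical analyses.** Between-group comparisons use the t test or Mann–Whitney test. For categorical variables, Chi-square or Fisher's "exact tests will be used to evaluate associations between categorical variables". For repeated data, "The generalized estimating equations test with Bonferroni adjustment will be used for comparison between variables during the study period". The section does not say which of these carries the primary comparison, and it gives no working correlation for the GEE.
- **Study protocol.** Body weight is measured at all nine visits, in both arms: "At each visit both groups are submitted to the research anthropometric tests and the 24-h recall diet is completed". The intervention arm has eight diet reinforcements and the control arm three to four.
- **Blinding.** Patients and dietitians are not blinded.

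**The concern.** Recruiting 120 instead of 98 protects power. It does nothing for validity if those who leave differ in weight course from those who stay, and differ in another way in the other arm. The methods named are exposed to this in two ways.

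- A t, Mann–Whitney or Chi-square test at month 12 has no value to use for a patient with no month-12 weight, unless one is imputed. It also ignores that patient's earlier weights.
- GEE does use the earlier weights of patients who leave. Without weighting, however, it is in general valid only if dropout does not depend on those weights, given the model covariates. How far it departs from this in practice depends on the working correlation.

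If intervention patients who are gaining weight leave more readily, and control patients leave for unrelated reasons, the diet looks better than it is. The reverse pattern hides a real effect.

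**Working it through.** **1. Reproduce the plan's figure.** Inputs from Sample size: difference 5, SD 8.8, α 0.05 (two-sided assumed), power 80%.

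n per arm = 2 × (1.960 + 0.842)² × 8.8² / 5² = 48.6, so 49 per arm and 98 in total. This matches. (One-sided α would give 78.)

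**2. Room for losses.** 120 − 98 = 22, and 22/120 = 18.3%. Check: 98/(1 − 0.183) = 120. If losses split evenly, that is 11 of 60 per arm.

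**3. Size of bias by simple arithmetic.** Suppose the patients lost from one arm would have differed from that arm's completers by D points at month 12, and losses in the other arm are unrelated to weight. Then bias = (share lost in that arm) × D.

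- D = 4.4 (half an SD): 11/60 × 4.4 = 0.8 points.
- D = 8.8 (one SD): 11/60 × 8.8 = 1.6 points.

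**4. Simulation with dropout driven by recorded weight.** These inputs are assumptions, not document figures: about 18% dropout per arm, related to weight in the intervention arm only, odds ratio 2.7 or 4.5 per SD of weight change. SD is 8.8. Two visit structures were tried:

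- (a) two visits, months 6 and 12, correlation 0.7, dropout depending on month-6 change;
- (b) eight post-baseline visits with random-walk covariance, dropout depending on current weight.

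Bias in the month-12 difference, in points (negative favours the diet):

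| Analysis | (a) two visits | (b) eight visits |
|---|---|---|
| Completers | −1.0 to −1.3 | −0.9 to −1.2 |
| GEE, independence | about as completers | about as completers |
| GEE, exchangeable | −0.05 to −0.2 | −0.4 to −0.6 |
| Likelihood mixed model | not run | about 0 |

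In (a), the completer t test has a false-positive rate of about 8.5% at odds ratio 2.7 and about 11% at 4.5, against a nominal 5%.

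Against the 5-point target, 0.9/5 = 18% and 1.3/5 = 26% for completers or independence GEE; 0.1/5 = 2% and 0.6/5 = 12% for exchangeable GEE.

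**5. Same relation in both arms.** With identical weight-related dropout in both arms, the bias is about 0 and the false-positive rate stays near 5%.

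**6. Dropout driven by the unseen month-12 weight itself.** With odds ratio 2.7 per SD in one arm, completer bias is about 1.5 points and the false-positive rate about 14%. Here the missing-at-random assumption fails, so the mixed model is not guaranteed to remove the bias.

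**The case against.** **Much of this is silence.** The article does not say that the tests are confined to patients weighed at month 12. It neither adopts nor excludes imputation, and a condensed article may leave analysis sets and missing-data rules to the full protocol or analysis plan. This stands: the silence is no finding, and a reader should not infer a declared completers-only analysis. What remains is that the methods the article does name are not, in general, valid under weight-related dropout.

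**The sample-size sentence is not wrong.** This also stands. It claims only to allow for dropouts, and it does. Reading 22 as an expected loss goes too far; it is headroom above the minimum.

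**GEE may be nearly unbiased.** With two visits and an exchangeable correlation, its bias was only 0.05 to 0.2 points. That is fair for that setting, but it does not carry over to eight post-baseline visits under the assumed covariance, where it was about 0.4 to 0.6. With an independence correlation there is no protection in either setting.

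**Differential dropout is assumed.** This stands. The article reports no dropout data. Research visits follow the same schedule in both arms and the diets are energy-matched; only the reinforcement differs. Extra support could just as well improve retention. Patients with anticipated difficulty of adherence are excluded from the start.

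**Worst-case bounds prove little.** A reader might assign all the missing patients to failure in one arm and success in the other and conclude that the under-5% result is uninterpretable. Such bounds need responder rates that the article does not give, and they would be wide in any trial with 18% missing. They are no evidence of a defect here.

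**Conclusion.** The point holds as a conditional weakness in the choice of method, with a cheap remedy. It is not a demonstrated error. The stronger reading, that the primary comparison is biased as planned, is not supported: it would need dropout related to weight in a way that differs between arms, and the article gives no evidence either way.

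If that dropout occurs at up to the level the sample size allows for, and with the assumed strength, the bias is roughly a fifth to a quarter of the target difference for completers or independence GEE. For exchangeable GEE it is between negligible and about an eighth of the target, depending on the visit structure assumed. Under the same relation in both arms it vanishes. The scale rests on the 18% loss, the one-arm selection, the odds ratios and the covariance structures, all of them assumed apart from the 22-patient allowance and the SD.

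Trial status reports sixty patients started and recruitment continuing, so the article describes a stage at which the analysis could still be settled without sight of the results. If the full protocol or analysis plan already does what follows, it is enough to say so.

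**What to change.** In Statistical analyses:

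1. **Weight.** Make the month-12 comparison a likelihood-based mixed model for repeated measures, with arm × visit, baseline weight and an unstructured covariance. Include all randomised patients in their assigned arm and use every visit weight. Report the month-12 contrast. This is valid when dropout depends on weights already observed.
2. **Under-5% outcome.** Multiply impute month-12 weight from the earlier visits, separately by arm, and then dichotomise. Add an analysis that counts a missing outcome as failure, as a sensitivity check.

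**Cost.** No extra patients, visits or measurements. SPSS can fit the mixed model; the imputation takes a little more programming. The downside is reliance on missing-at-random, which the data cannot verify. If patients leave because of weight changes never recorded, some bias can remain, so the assumption should be stated beside the result.
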